# Platelet inhibition during ticagrelor monotherapy versus ticagrelor plus aspirin in patients with coronary artery disease (TEMPLATE study): study protocol for a randomised controlled trial

**DOI:** 10.1186/s13063-017-2277-9

**Published:** 2017-11-09

**Keywords:** Antiplatelet therapy, Platelet function, Haematology, Ticagrelor, Clopidogrel, Prasugrel, Aspirin, P2Y_12_ blocker

## Abstract

**Background:**

Dual antiplatelet therapy (DAPT) with aspirin (ASP) and a P2Y_12_ blocker is currently standard care after percutaneous coronary intervention (PCI) with stent insertion, and aims to inhibit platelet function in order to prevent stent thrombosis. The P2Y_12_ blocker ticagrelor (TIC) has greater antiplatelet effect than the previously used members of this class, such as clopidogrel. In healthy volunteers, TIC is sufficient to cause strong platelet inhibition, with little additional effect from ASP. Omission of ASP may improve the safety of antiplatelet regimes by reducing bleeding. However, the effect of single antiplatelet treatment with TIC, compared to DAPT with TIC + ASP, has not been studied in detail in patients with coronary artery disease.

**Methods:**

To compare TIC with TIC + ASP, we have initiated a single centre, open-label randomised controlled trial (TEMPLATE study) in adults receiving DAPT following PCI with a sample size of 110 patients. Patients are invited to join the study when, as part of standard care, they are due to switch from DAPT (ASP + any P2Y_12_ blocker) to single antiplatelet treatment with ASP alone after 6–12 months. Patients are randomised to receive either TIC or TIC + ASP for 4 weeks. All patients then revert to standard care with ASP alone. Blood samples and clinical data are collected at three study visits: at baseline during treatment with ASP + any P2Y_12_ blocker (visit 1); approximately 4 weeks after visit 1 during treatment with either TIC or TIC + ASP (visit 2); and approximately 8 weeks after visit 1 when treatment has reverted to ASP alone (visit 3). The primary outcome is the extent of platelet inhibition, measured by light transmission aggregation, flow cytometry, flow chamber and plasma biomarker tests. The primary analysis will compare the extent of platelet inhibition between the TIC and TIC + ASP groups at visit 2, adjusted for baseline platelet reactivity. Secondary analyses will compare the extent of platelet inhibition at visit 2 with that at visit 3.

**Discussion:**

This is the first study to compare in detail the extent of platelet inhibition in patients who are receiving TIC compared with TIC + ASP. The study findings will complement larger-scale trials of the clinical efficacy and safety of TIC compared to TIC + ASP.

**Trial registration:**

ISRCTN registry, identifier ISRCTN84335288. Registered on 23 June 2014.

**Electronic supplementary material:**

The online version of this article (doi:10.1186/s13063-017-2277-9) contains supplementary material, which is available to authorized users.

## Background

Dual antiplatelet therapy (DAPT) with aspirin (ASP) and a P2Y purinoreceptor (P2Y_12_) blocker is standard care for patients with coronary artery disease in several settings, including after acute coronary syndrome (ACS) and percutaneous coronary intervention (PCI) with or without coronary stent insertion [1–3]. The rationale for this treatment is that most adverse cardiac events that occur in these settings result from the formation of abnormal platelet aggregates causing coronary artery or stent thrombosis. Inhibition of platelets by simultaneously targeting both the thromboxane A_2_ pathway (with ASP) and the P2Y_12_ receptor pathway (with a P2Y_12_ blocker) results in strong platelet inhibition and helps prevent aggregate formation [2]. The intensity of antiplatelet treatment is typically reduced at 6–12 months following ACS or PCI by switching patients from DAPT to single-agent treatment with ASP alone. This ensures strong platelet inhibition in the highest risk period after ACS or PCI and minimises the long-term bleeding risk associated with DAPT.

When used in combination with ASP, clopidogrel (CLOP; the first widely used P2Y_12_ blocker) reduced the incidence of major adverse cardiac events compared to single antiplatelet treatment with ASP [4]. However, approximately 30% of individuals display incomplete inhibition of the platelet P2Y_12_ receptor pathway with CLOP, resulting in reduced efficacy [5]. These limitations have been circumvented by the development of strong P2Y_12_ blockers such as ticagrelor (TIC), which give greater and more consistent inhibition of the P2Y_12_ receptor pathway compared with CLOP. Accordingly, TIC in combination with ASP is associated with fewer major adverse cardiac events than CLOP in combination with ASP [6].

More recent observations made in experimental models of platelet inhibition [7] and in observational studies of healthy volunteers receiving antiplatelet treatments [4] suggest that strong P2Y_12_ blockers such as TIC used alone result in a consistent and full platelet inhibition, and that little further platelet inhibition is achieved by the addition of ASP. In response to these findings, it has been proposed that medication with strong P2Y_12_ blockers without additional ASP may be sufficient to achieve full therapeutic antiplatelet effect in clinical settings in which DAPT is currently standard care [8]. Avoidance of ASP may also confer safety benefits because ASP is associated with gastrointestinal bleeding due to its local effect on gastric mucosa, unrelated to the antiplatelet effect [9].

Single antiplatelet treatment with TIC is currently being evaluated in the GLOBAL LEADERS study, which is a large, international, multicentre, randomised controlled trial of TIC versus TIC + ASP following PCI and coronary stent insertion [10]. However, the main endpoints of this trial are all-cause mortality or non-fatal myocardial infarction and bleeding. The GLOBAL LEADERS study does not include a detailed laboratory evaluation of the pharmacodynamic effect of the two different treatment regimes on platelet inhibition.

## Aims and objectives

The main aim of the TEMPLATE study is to determine the extent of platelet inhibition in patients with coronary artery disease achieved with single antiplatelet treatment with TIC compared with DAPT with TIC + ASP. The secondary aim is to compare the effect of TIC or TIC + ASP to single antiplatelet treatment with ASP alone.

The study objectives are to perform laboratory measurements of platelet inhibition in patients at the following points of treatment with antiplatelet drugs after PCI: (i) at the end of DAPT with ASP + any P2Y_12_ blocker treatment; (ii) after 4 weeks of treatment with either TIC or TIC + ASP; and, (iii) after all patients are switched to ASP alone after the study intervention.

## Methods

### Study design and setting

The TEMPLATE study is a single centre, open-label, randomised controlled trial of the effects of different antiplatelet treatments on platelet laboratory test results in patients who have undergone PCI and coronary stent insertion at the Bristol Heart Institute (BHI).

### Study population

The study population is patients at the BHI who have been prescribed DAPT as part of standard clinical care following PCI and coronary stent insertion.

A patient will be eligible for inclusion if: (i) prescribed DAPT with ASP + any P2Y_12_ blocker for a minimum interval of 4 weeks; and (ii) intending to transfer to ASP after cessation of treatment with ASP + any P2Y_12_ blocker; and, (iii) aged over 18 years at the point of randomisation.

Patients will be ineligible if any of the following apply: (i) contraindication to DAPT; (ii) treatment with ASP + any P2Y_12_ blocker after PCI was interrupted or terminated because of bleeding or increased bleeding risk; (iii) contraindication to TIC; (iv) pregnancy and or breast feeding; (v) the patient is a woman of childbearing potential who is unwilling to use contraception; (vi) the patient is a man with a spouse or partner with childbearing potential unless the patient is sterilised or has agreed to use barrier contraceptives.

Concomitant medications which may modify the therapeutic effect of TIC or which may have their therapeutic effect modified by TIC are not absolute exclusions to the study, but will be considered as potential reasons for exclusion by the enrolling clinician. These include: (i) strong CYP3A4 inducers (e.g. rifampicin, dexamethasone, phenytoin, carbamazepine and phenobarbital), (ii) CYP3A4 substrates with narrow therapeutic indices (e.g. cisapride, ergot alkaloids, simvastatin or lovastatin, (iii) digoxin, and (iv) potent P-glycoprotein inhibitors (e.g. verapamil, quinidine, cyclosporin).

Concomitant medications with a potential adverse interaction when co-prescribed with ASP will be considered as potential reasons for exclusion by the enrolling clinician. These include: some diuretics, probenecid, heparin, phenindione, antiepileptics such as phenytoin, warfarin, insulin and sulphonylurea hypoglycaemic agents, non-steroidal anti-inflammatory drugs, methotrexate, corticosteroids, antacids, iron salts, carbonates, alkali hydroxides and ibuprofen.

### Patient approach and study visits

Potentially eligible patients will be identified using hospital databases which record the demographic details of patients who undergo interventional cardiology procedures at the BHI and the antiplatelet treatment prescribed after the procedure. The first approach will be an invitation letter and patient information leaflet. Since most patients in the study population were receiving DAPT for 6–12 months, this was usually sent by post approximately 6 weeks before the planned completion of DAPT. Potentially eligible patients who reply expressing an interest in taking part will be contacted by telephone and invited to attend three outpatient study visits at the BHI. They will be instructed to continue with their existing DAPT until the first study visit. A study flow diagram is shown in Fig. 1.

**Fig. 1 Fig1:**
[figure not shown]
Trial schema. Schema showing the recruitment pathway with the number of patients to be recruited, anticipated eligibility, recruitment and follow-up rates. *ASP* aspirin, *CLOP* clopidogrel, *TIC* ticagrelor

At each of three study visits, clinical data will be collected and an 18 mL venous blood sample will be obtained by peripheral venepuncture for laboratory analysis. The schedule of data collection is shown in Fig. 2. All data will be collected on a bespoke database and stored on a secure server.

**Fig. 2 Fig2:**
[figure not shown]
Schedule of data collection (SPIRIT)

## Study visit 1

Study visit 1 will occur when a patient would be switching from DAPT with ASP + any P2Y_12_ blocker to ASP alone in the standard clinical care pathway. A member of the research team will describe the study, answer questions and confirm eligibility. Eligible patients will be invited to complete and sign the study consent form.

### Randomisation

Allocation to the TIC + ASP group or the TIC group in a 1:1 ratio will be performed by an authorised member of the research team using a secure internet-based randomisation system (http://www.sealedenvelope.com/), using block randomisation with blocks of varying sizes. Clinicians, research nurses, trial coordinators, pharmacists and patients will be aware of the allocation. As the trial is open label, no code-breaking procedure is required. Since the costs associated with production of a placebo medication were prohibitively high, we adopted a pragmatic open-label design in which the study patients, their clinicians, research nurse and trials coordinator will not be blinded to treatment allocation. We do not anticipate this to have a significant impact on trial results. The laboratory staff will be blinded to group allocation.

### Trial interventions

Patients randomised to the TIC + ASP group will transfer from ASP + any P2Y_12_ blocker to ASP 75 mg once per day plus a loading dose of TIC 180 mg followed by TIC 90 mg twice per day. Patients randomised to the TIC group will transfer from ASP + any P2Y_12_ blocker to a loading dose of TIC 180 mg followed by TIC 90 mg twice per day. The study medication will continue to be taken until study visit 2 at 28 days (acceptable range 21–35 days) after enrolment and randomisation. The study medication will be stored and dispensed by the trial site’s pharmacy in accordance with Good Clinical Practice. Patients will be asked to record any missed doses, and to return any unused medication at their second study visit to ascertain adherence. Patients will be instructed to take the next scheduled dose as usual, if they miss a dose.

## Study visit 2

Patients will be interviewed by the study team to collect safety data and to check compliance with the study medication (Fig. 2). The safety data will include adverse events potentially associated with the study medication, the occurrence of major adverse cardiac events and bleeding, categorised using the Bleeding Academic Research Consortium (BARC) definitions of bleeding (Table 1) [11].

**Table 1 Tab1:** Bleeding Academic Research Consortium (BARC) definitions

Class	Definition
Type 0	No bleeding.
Type 1	Bleeding that is not actionable and does not cause the patient to seek unscheduled performance of studies, hospitalisation, or treatment by a healthcare professional; may include episodes leading to self-discontinuation of medical therapy by the patient without consulting a healthcare professional.
Type 2	Any overt, actionable sign of haemorrhage (e.g. more bleeding than would be expected for a clinical circumstance, including bleeding found by imaging alone) that does not fit the criteria for type 3, 4, or 5 but does meet at least one of the following criteria: requiring nonsurgical, medical intervention by a healthcare professional, leading to hospitalisation or increased level of care, prompting evaluation.
Type 3a	Overt bleeding plus haemoglobin drop of 3 to < 5 g/dL, corrected for transfusion (provided haemoglobin drop is related to bleed) OR any transfusion with overt bleeding.
Type 3b	Overt bleeding plus haemoglobin drop < 5 g/dL, corrected for transfusion (provided haemoglobin drop is related to bleed) OR cardiac tamponade. Bleeding requiring surgical intervention for control (excluding dental/nasal/skin/haemorrhoid) OR bleeding requiring intravenous vasoactive agents.
Type 3c	Intracranial haemorrhage (does not include microbleeds or haemorrhagic transformation, does include intraspinal) Subcategories confirmed by autopsy or imaging or lumbar puncture OR intraocular bleed compromising vision.
Type 4	Coronary artery bypass graft (CABG)-related bleeding OR perioperative intracranial bleeding within 48 h OR reoperation after closure of sternotomy for the purpose of controlling bleeding OR transfusion of ≥ 5 U whole blood or packed red blood cells within a 48 h period (cell saver product are not included) OR chest tube output ≥ 2 L within a 24-h period.*
Type 5a	Probable fatal bleeding; no autopsy or imaging confirmation but clinically suspicious.
Type 5b	Definite fatal bleeding; overt bleeding or autopsy or imaging confirmation

*If a CABG-related bleed is not adjudicated as at least a type 3 severity event, it will be classified as not a bleeding event. If a bleeding event occurs with a clear temporal relationship to CABG (i.e. within a 48-h time frame) but does not meet type 4 severity criteria, it will be classified as not a bleeding event

All patients will then be transferred to ASP 75 mg once per day, thereby returning to standard clinical care. This treatment will continue until study visit 3 which will be 28 days (acceptable range 21–35 days) after study visit 2, and thereafter, long-term. Patients who are unable to attend study visit 2 within 35 days from study visit 1 will be advised to transfer to ASP 75 mg once per day at 35 days after study visit 1 and will be invited to attend for a final study visit at the same time as their planned study visit 3.

## Study visit 3

Patients will be interviewed by the study team to collect safety data and to check compliance with the prescribed medication. Patients will then exit the study and will be instructed to continue ASP 75 mg once per day as per standard clinical care under the ongoing supervision of their primary care practitioner (Fig. 2).

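### Table 1 prints the haemoglobin limit for BARC type 3b as a fall below 5 g/dL, which contradicts type 3a and can misgrade bleeding safety data

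*Protocol article*

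**What the plan says.** Under Study visit 2, safety data are collected by interview and bleeding is to be "categorised using the Bleeding Academic Research Consortium (BARC) definitions of bleeding (Table 1" of the article, with a citation to the published definition). Three rows of that table matter here.

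- Type 3a: "Overt bleeding plus haemoglobin drop of 3 to < 5 g/dL, corrected for transfusion". It has a second route: "OR any transfusion with overt bleeding".
- Type 3b: "Overt bleeding plus haemoglobin drop < 5 g/dL, corrected for transfusion". Its other routes are cardiac tamponade, surgery to control the bleed (with some minor sites excepted) and the need for intravenous vasoactive drugs.
- Type 2: an overt, actionable bleed "that does not fit the criteria for type 3, 4, or 5 but does meet at least one of the following criteria".

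No other part of the article restates or corrects the 3b limit.

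**The concern.** Type 3b is the next grade up from 3a, yet it is printed with the same upper limit and no lower limit. The more severe grade therefore takes in every fall that defines the less severe one, together with all smaller falls, and leaves out the largest. Because the text names this table as the basis for categorising bleeds, anyone who grades from it as printed can put a bleed in the wrong class. Clinicians and research nurses know the allocation (Randomisation section), so an overlap between two grades also leaves a choice to unblinded staff.

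**Working it through.** No figure in the sample size or analysis sections is involved. The check is a comparison of intervals. Let d be the haemoglobin fall in g/dL, corrected for transfusion and related to an overt bleed.

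Inputs, all from Table 1:
- 3a as printed: 3 ≤ d < 5
- 3b as printed: d < 5, with no lower bound
- 3b if it starts where 3a stops: d ≥ 5 (an inference from the 3a limit)

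| d (g/dL), values tried | Haemoglobin class as printed | Haemoglobin class with 3b as d ≥ 5 |
|---|---|---|
| 0.5, 1, 2, 2.9 | 3b only | none |
| 3, 4, 4.9 | 3a and 3b | 3a only |
| 5, 5.1, 6, 8 | none | 3b only |

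As printed, the intersection of 3a and 3b is [3, 5), which is the whole of 3a. The range with no haemoglobin class is d ≥ 5.

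Three consequences follow from the rows read together.

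1. **Falls of 3 to under 5.** Both rows apply. If a grader takes the higher grade, the 3a haemoglobin criterion never decides anything.
2. **Falls below 3.** Such a bleed fits 3b. Type 2 excludes bleeds that fit type 3, so an actionable bleed with a measured, related fall of 1 g/dL would move from type 2 to 3b.
3. **Falls of 5 or more.** Neither haemoglobin criterion applies. With a transfusion the bleed reaches 3a. With tamponade, surgical control or vasoactive drugs it reaches 3b. With none of these, and no criterion of 3c, 4 or 5, it drops out of type 3. An actionable bleed with d = 6 could then be type 2 while one with d = 1 is 3b.

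A symbol lost in reading the PDF is an unlikely cause. A definite less-than sign is printed in the 3b row, and the greater-or-equal sign is intact in the type 4 row of the same table: "transfusion of ≥ 5 U whole blood or packed red blood cells within a 48 h period". A look at the printed article would settle it.

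**The case against.** The contradiction between the two rows is hard to dispute. The case on the other side concerns how much follows from it, and most of that case stands.

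- A reader might infer that the error spoils a safety comparison between the arms. The article describes none based on bleeding grade. The primary and secondary outcomes are all laboratory tests, and the comparisons in the Statistical analysis section concern those results. Reduced bleeding is part of the motivation, but the stated aim is the extent of platelet inhibition.
- A reader might infer that safety monitoring is distorted. The Statistical analysis section has the trial management group watch the rate of adverse events against an expected rate, without reference to BARC grade. A misgraded bleed still counts once. The rule for stopping study medication, in the section on loss to follow-up and withdrawals, does not use BARC type either.
- A reader might infer that every small bleed moves up to 3b. That needs a measured haemoglobin fall related to the bleed. Type 1 bleeds by definition prompt no unscheduled tests, and the Laboratory analyses section lists no haemoglobin. The data collection schedule (Fig. 2) is not shown, so this cannot be settled. A move up from type 2 is possible; from type 1 it is improbable on the visible text.
- The text also cites the external BARC definition, and nothing shows that the misprint reached the full protocol, the case report form or the database. This is fair, and it is why a check is asked for and no actual misgrading is asserted.

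What does not stand is any suggestion that the row is harmless background. It is a classification limit in the table named for grading the trial's bleeds.

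**Conclusion.** The point holds as an internal contradiction in Table 1. Row 3b as printed contains all of 3a, takes in falls below 3 g/dL and excludes falls of 5 g/dL or more. Its reach is the grading of bleeding safety data and nothing further. The article gives no expected bleeding rate, so the number of bleeds affected cannot be estimated. With 110 patients followed for about 8 weeks it is likely to be small.

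The conclusion rests on two assumptions: that the less-than sign is in the published table, and that 3b was meant to begin at the upper limit of 3a. The second is inferred from the ordering of the rows, since the cited definition is not at hand.

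**What to change.** Correct the haemoglobin criterion in the type 3b row so that it starts where 3a stops. The inferred wording is a fall of ≥ 5 g/dL, to be confirmed against the cited BARC definition. The haemoglobin ranges from 3 g/dL upward are then non-overlapping and complete.

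This does not make rows 3a and 3b mutually exclusive in every respect: a transfused bleed with a fall of 5 g/dL or more would still meet 3a by transfusion and 3b by haemoglobin. Falls below 3 g/dL would meet neither haemoglobin criterion.

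Then check whether the case report form and the database coding carry the same limit, and re-grade any bleed already classified under the printed row. Recruitment was still open when the article was written. The cost is one symbol in a table, a short check of the form and database, and a review of any bleeds graded so far.

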### Definition of end of trial

Patients will end their involvement in the study after they have completed study visit 3, at approximately 8 weeks after study visit 1. The end of the study is when analyses of blood samples are completed, data queries are resolved, the database is locked and the analysis completed.

### Loss to follow-up and withdrawals

Each patient has the right to withdraw at any time. In this event, we will analyse any data already collected, unless the patient expresses a wish for their samples to be destroyed and any associated data not to be included in the analysis. We expect low rates of patient withdrawal and losses to follow-up because the study interval is only approximately 8 weeks and requires only three study visits. It is also unlikely that patients will have to be withdrawn from their allocated study treatment as the study intervention (TIC + ASP or TIC) is well tolerated and is prescribed for only a 4-week period. However, in the event of a serious adverse event that the investigator believes may be attributable to the intervention, the study medication will be discontinued and the patient will be returned to standard care with ASP 75 mg once daily. The trial medication may also be discontinued if any contraindicated therapy is initiated whilst the patient is participating in the trial. Data collected before discontinuation of trial medication will be included in the analyses.

